### Pre-delivery screening

In both Route 1 and Route 2 enrolment, mothers must provide written consent before assessment of personal information (antenatal card) and questioning can begin. After consenting, mothers will be asked for their demographic information and their personal contact details. Pregnant mothers will be excluded from the study if they are below the age of 18 years, have no foetal heartbeat detected upon admission, known to be HIV-positive, in receipt of
*Mycobacterium tuberculosis* therapy, taken antibiotics in the last 24 hours, had a blood transfusion in the last month, suffering from severe pre-eclampsia or antepartum haemorrhage, or in another research study. Mothers can refuse to be part of the study at any stage of the study protocol. Pregnant women that are referred at this point to a tertiary level healthcare facility, will be excluded from the study.

### Delivery procedures, post-delivery screening and umbilical cord blood collection

***Delivery procedures and screening.*** Study nurses will assist clinical KGH maternity ward staff in the delivery process and collect data via electronic case report form (eCRF) on their designated study tablets. Neonates will be excluded at the delivery stage of the study for the following reasons: major congenital malformations (not including polydactylism), blood transfusions given to mother or neonate, severe birth asphyxia (requiring resuscitation), neonates born via breech, vacuum or via caesarean section, or a birthweight <2000g. After the delivery stage of the study protocol, neonates can be excluded from the study following the detection of infection or illness (information gained from full blood count analysis or review of systems). Neonates will also be removed from the study protocol, if medication is given (not including intramuscular vitamin K, tetracycline eye ointment or any immunisations). All medication that is given to mothers and neonates will be recorded. Mothers will be able to refuse study participation at any stage. Mothers that deliver multiple newborns will only be invited to consent and enrol one of their neonates into the study.

***Umbilical cord blood collection.*** Once the neonate is fully delivered, one-minute delayed cord clamping will be used (following World Health Organisation (WHO) policy
^52^). During the one-minute delay, the one-minute APGAR score will be conducted. If the neonate requires resuscitation, the neonate will be excluded from the study. After the umbilical cord has been removed and cleaned, a trained study nurse will identify the umbilical arteries and the umbilical vein. Blood will be collected from both. The tubes will be placed in the cool box for 1–6 hours before transfer to the study laboratory for primary processing. If the mother is enrolled by route 2, the mother will be asked to provide written consent to full study recruitment before the sample is sent for primary laboratory processing. The time between the collection and the processing of blood samples will be recorded and analysed.

### Hospital assessment and 1
^st^ venous blood draw

***Hospital health assessment (study recruitment and group allocation).*** At 6–24 hours post-delivery, recruited mothers and their neonates will be invited to a private consultation with the study research clinician. Further demographic data will be collected, along with a photograph of the antenatal card to gather gestational age data (fundal height, last menstrual period and ultrasound), mother’s last haemoglobin level before delivery (dated), known sickle cell status, neonate immunisations, and medication given to the mother (pre, during and post-delivery) and the neonate. A complete review of systems of the mother and neonate plus anthropometric data on the newborn will then be collected. Neuromuscular and physical maturation of each neonate will be assessed using the New Ballard Score
^48^.

Neonates will be excluded if they score less than 32 weeks of gestation. From this assessment, the neonate will be assigned to a specific study group. If the neonate is allocated to the Group D (FTB+NBW) group, the neonate will be allocated to a randomised bleed group (≥24 hours - <80 hours (Group D1); ≥80 hours - <136 hours (Group D2); and ≥136 - <192 hours (Group D3). Failure to meet the inclusion criteria at this stage of the study protocol, will result in exclusion from the study.

According to current practice, at-birth vaccination of neonates at Kanifing General Hospital (The Gambia), does not occur until a later time point in the first week of life due to social and logistical reasons. However, mothers will still be asked whether the neonate has been vaccinated prior to the health assessment before the 1
^st^ venous bleed takes place. The answers will be recorded and analysed.

***1
^st^ venous blood draw (all neonates).*** A blood sample will be collected from all neonates that have passed the inclusion criteria in the hospital health assessment. Immediately after the health assessment, a venous blood draw will be performed (6–24 hours post-delivery). PTB and/or LBW neonates will donate 2ml of venous blood. FTB+NBW neonates will donate 3.5ml of venous blood. All samples will reach the laboratory within three hours post collection for primary processing.

### Community health assessment and 2
^nd^ venous blood draw

***Community health assessment.*** Study nurses will visit all mothers or enrolled neonates at their homes at least once. At that visit, a physical examination of the neonate will be completed. The following information will also be collected: neonatal immunisation history (date, time and type), a complete review of systems of the mother and baby, and any medication given to the mother or neonate since delivery. Mothers will also be provided with health education and study contact details (should the neonate become unwell). The effect of vaccination on iron and inflammatory parameters in the first week of life will be analysed as part of the formal data analysis plan.

***2
^nd^ venous blood draw Group D (FTB+NBW) only.*** At this point, if the mother and neonate are deemed to have passed the screening process and the neonate is in Group D, then the neonate will have its second and last venous blood draw (3.5ml). All samples will reach the laboratory within three hours post collection for primary processing.

### Laboratory evaluations

***Blood samples.*** The processing of samples will be conducted 1-6 hours after collection to allow serum samples to coagulate and to allow mothers admitted via route 2 to give written consent. On arrival to the laboratory, whole blood samples in 4.5ml Sarstedt S-Monovette K3E (SARSTEDT AG & Co. KG, Germany) will be inverted five times and assessed for a full haematology panel using a Medonic M20M GP (Boule Diagnostics, Spanga, Sweden). The remaining whole blood sample will be aliquoted into 2ml Sarstedt micro tubes (SARSTEDT AG & Co. KG, Germany) and frozen at -20°C. Glucose-6-phosphate dehydrogenase deficiency testing (R&D Diagnostics Limited, Papagos, Greece) and sickle trait will be conducted at the end of the recruitment period of the study.

The Sarstedt S-Monovette Serum-Gel blood collection tube (SARSTEDT AG & Co. KG, Germany) will be centrifuged at 3500rpm for 10 mins using an Eppendorf Centrifuge 5702 (Eppendorf, Germany). Serum will be aliquoted into 2ml Sarstedt micro tubes (SARSTEDT AG & Co. KG, Germany), boxed and labelled before being stored at -20°C until after the recruitment period. The laboratory analysis of all serum samples will be conducted as one batch. All serum samples collected will be assessed by ELISA for the following: IL6, IL22, free haem, hepcidin, hemopexin, lipocalin-2, lactoferrin, and foetal haemoglobin. DRG Hepcidin 25 (bioactive) HS ELISA (EIA-5782) (dynamic range: 0.135 - 81 ng/mL), made by DRG Instruments GmbH, Germany, will be used to measure serum hepcidin. Additionally, serum ferritin, serum iron, UIBC, soluble transferrin receptor (sTfR), transferrin, C-reactive protein (CRP), haptoglobin, and alpha 1-acid glycoprotein (AGP) will be assessed using a fully automated biochemistry analyser (Cobas Integra 400 plus). Furthermore, umbilical WBC will be processed and analysed for exploratory secondary analysis 4.

***Bacterial growth assays.***
*Ex vivo* growth of bacteria (including clinical and laboratory isolates of
*Staphylococcus aureus, Klebsiella pneumoniae, Escherichia coli, Enterobacter* spp.
*, Enterococcus* spp., and
*Salmonella* Typhimurium) in a 1:1 mixture of participant serum and Iscove’s Modified Dulbecco’s Medium (IMDM, Invitrogen) as in [name]
*et al.* (2015)
^53^ will be performed.

### Study outcomes

The primary outcome variables will be TSAT (transferrin saturation) and serum iron.

The secondary outcome variables will be hepcidin; hemopexin; haptoglobin; IL22; free serum haem and haemoglobin; foetal haemoglobin; lactoferrin; lipocalin-2; IL6; C-reactive protein; alpha-1-acid glycoprotein; transferrin concentration; soluble transferrin receptor; unbound iron-binding capacity; ferritin; haemoglobin; WBCs types and numbers in cord blood samples and
*ex vivo* bacterial growth.

### Data entry, handling, storage and security

All protocol-required field data will be captured electronically on an electronic eCRF or a paper case report form (CRF) that will be completed for each included participant. After giving written consent the pregnant women will be given a study identification number, which will be used in all future datasets for subject anonymity. Field data will be collected verbally and from antenatal cards by study nurses. Collected data will be entered in real time using eCRFs developed on top of a
REDCap (Research Electronic Data Capture) database and published on Samsung Galaxy Tab 3 SM-T111 handheld devices. Collected data will be transported to the database via a direct secure connection over the 4G mobile network. Laboratory related data will be extracted directly from laboratory equipment and uploaded to the database. Any data collected on the paper format will be double entered by a trained data entry clerk. The local co-investigator will review all forms and identify any errors prior to data entry or to marking data as complete. The study data will also be validated through automated and manual validation methods implemented in the study database application system. The study database will be custom-developed. All paper CRF will be stored in a locked file archive. Electronic data will be stored on the local dedicated server maintained at MRCG. The study will be conducted in compliance with Good Clinical Practice. Study personal security measures will include controlled access limited to authorised users only, physical security, remove identifiable information (anonymization), avoidance of third-party cloud storage and password protection.

### Sample size and power

This study will target recruitment of 150 ‘’exposed” neonates which will include a target of 50 neonates in each Group A, B and C. 300 neonates will be recruited for Group D (“unexposed”). The study will have constraints from time, budget, loss to follow up, haemolysis during sample collection, insufficient blood volume and the distribution of new births in each group at the Kanifing General Hospital. 

Based on this, we have run simulations (
Stata/IC 15.1) to calculate the power to detect a range of differences comparing groups for example Groups D and A with respect to the primary outcomes TSAT and serum iron. We did not calculate power for the secondary outcomes, which are considered exploratory. The simulation was run using a linear regression model assuming a lognormal distribution for the response variables TSAT and serum iron levels 6–24 hours after birth. Data from a previous study ([name], personal communication) was used to obtain mean and SD estimates for TSAT and serum iron both at baseline and 6–24 hours after birth. The predictor variables were the Groups (A–D) with Group D as the reference. The model was adjusted for the baseline (cord blood levels). We also examined the power assuming a normal distribution for TSAT (i.e. without log transformation). The significance level considered was 0.05 and the simulation was run for 100000 iterations. This process was repeated for the following four different sample size scenarios which we refer to as
*N1*,
*N2*,
*N3* and
*N4* respectively:

*N1*) Group
*A*=Group
*B* =Group C =50 neonates
*N2*) Group
*A*=Group
*B* =25 neonates and Group C =50 neonates
*N3*) Group
*A*=Group
*B* =10 neonates and Group C =50 neonates
*N4*) Group
*A*=Group
*B* =50 neonates and Group C =10 neonates

For all the above four cases,
*D*=300.

The simulation results for the baseline adjusted model with log transformation show that for sample size scenario
*N1*, the minimum mean differences that can be detected with 80% power were about 4% and 2.5 μmol/L for TSAT and serum iron respectively (
Figure 3A and 3B). These correspond to effect sizes of 0.35 and 0.39 respectively. The power drops substantially if smaller numbers were to be recruited as in scenarios
*N2* (
*A*=
*B*=25) and
*N3* (
*A*=
*B*=10). Under
*N2* and
*N3*, the minimum mean differences that can be detected with 80% would increase to about 5.8% and 9.1% for TSAT (
Figure 3A) and 3.3 μmol/L and 5 μmol/L for serum iron (
Figure 3B). The results for scenario
*N4* can be considered as subset of
*N1*-
*N3* by rearranging Groups A, B and C.

**Figure 3. f3:**
[figure not shown]
Estimated power to detect a given difference between Groups
*A* vs
*D* based on simulation using a linear regression model adjusted for baseline for three sample size scenarios. *N1* (Group A=Group B=Group C=50 neonates);
*N2* (Group
*A*=Group
*B* =25 neonates and Group C=50 neonates);
*N3* (Group
*A*=Group
*B* =10 neonates and Group C=50 neonates);
*N4* (Group
*A*=Group B=50 neonates and Group C =10 neonates).

### Statistical analysis

The primary research objective is to examine if preterm and/or low birthweight neonates (“Exposed”) have a reduced ability to sequester iron at 6–24 hours after birth in comparison to full term neonates with normal birthweight (“Unexposed”)?

We hypothesize that FTB+NBW (Group D) neonates on average will have lower values of TSAT and serum iron compared to “Exposed” (PTB or LBW babies) (
Figure 4). Initially, we will analyse all “Exposed” (Groups A+B+C) vs “Unexposed” (Group D). Each neonate will be further classified by his or her gestational age (premature vs. full term) and birthweight (low vs. normal) in a 2x2 table (
Table 1). Linear regression models will be used in order to evaluate the difference in mean between each Group A–C and D; that is where
*D* will be the reference group. TSAT and serum iron levels will be log transformed before fitting the models (if necessary). Both the unadjusted and adjusted (for the cord blood level) mean differences together with the 95% CI will be calculated.

**Figure 4. f4:**
[figure not shown]
An example of hypothetical scenario for TSAT values between the groups to be compared. In this example: (i) Time 0 refers to average cord blood levels (ii) Time 6–24 refers to the mean level in the 6–24 hour period after birth. (iii) T1, T2, represent TSAT in 1 and 2 above and ΔT=T2-T1 for full term, normal birthweight (Group D) (iv.) T1’, T2’and ΔT’=T2’-T1’ same as above but for the premature, low birthweight (Group A). Hypothesis: H
_0_: T2=T2’ vs. H
_A_: T2≠T2’.

**Table 1. T1:** Four combinations in total for exposure:
*a*: Pre, Low;
*b*: Pre, Normal;
*c*: Full, Low and
*d*: Full, Normal.

		Birthweight (BW)	
		Low	Normal
Term	**Pre**	A	B
	**Full**	C	D

In the second stage of analysis, we will assess the effect of potential confounding variables using the regression models. Covariates to be considered include the specific time of measurement, demographic and health variables. The time effect may not be linear, and this will be investigated in the further regression models. To reduce the effects of multiple testing, data analysis will be driven by a predefined primary study hypothesis. Any exploratory analyses conducted (in the absence of predefined study hypotheses) will be considered hypothesis-generating, rather than confirmatory. In order to reduce the levels of missing and inaccurately entered data into the database, all clinical, demographic and laboratory data will be entered in real time via electronic data capture, with automated and manual validation methods implemented. The study design does not provide for the recruitment of equal numbers of subjects in each month of the year (or during the dry vs wet seasons). The Gambia has a higher birth rate during the months of September–December in comparison to other months
^54^.

In order to remove this potential source of bias, we will adjust for month of birth and/or season in the regression analysis. If the missing data rates is more than 5%, we will consider imputation. The follow-up duration is relatively short. Thus, we expect little bias from loss to follow-up. If loss to follow-up rate is considerably different between groups, we will perform sensitivity analyses to examine the robustness of results. We will also consider sensitivity analysis fitting a multivariate regression model where the main outcomes of interest (including TSAT, serum iron and hepcidin) will be jointly regressed to the same set of predictors.

The analysis for the secondary objectives are described below:

I. 
**Characterise how iron metabolism, handling and recycling differs between full term, preterm and low birthweight neonates at birth and during the first 24 hours of life.**

A similar strategy will be used as for the primary objective. Regression modelling will be used to evaluate the difference in means between each Group A–C and D; D will be the reference (“Unexposed”) group. The effects of potential confounding variables will also be assessed using further regression modelling.

II. 

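### The multivariate regression named as a sensitivity analysis uses the same predictors for every outcome, so it cannot test the robustness of the TSAT or serum iron estimates

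*Protocol article*

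**What the plan says.** All references are to the protocol article.

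- **Primary analysis (Statistical analysis).** "Linear regression models will be used in order to evaluate the difference in mean between each Group A–C and D", with D as reference. Exposed babies (A, B and C together) are first compared with D. TSAT and serum iron are log transformed if needed. Mean differences with 95% confidence intervals are given unadjusted and adjusted for the cord blood level.
- **Sensitivity analyses (same section, after Table 1).** One is conditional on loss to follow-up differing between groups. The other, which the authors undertake only to consider, is a multivariate model "where the main outcomes of interest (including TSAT, serum iron and hepcidin) will be jointly regressed to the same set of predictors".
- **Design (Sample size and power).** The exposed groups have "a target of 50 neonates in each Group A, B and C", and "300 neonates will be recruited for Group D". On the level and power, the text says "The significance level considered was 0.05 and the simulation was run for 100000 iterations" and "the minimum mean differences that can be detected with 80% power were about 4% and 2.5 μmol/L for TSAT and serum iron respectively".

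The article names no variance estimator and gives no SD by group.

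**The concern.** A sensitivity analysis should be able to give a different answer when an assumption of the main analysis fails. A joint linear regression of several outcomes on identical predictors changes none of the assumptions behind each outcome's estimate. If it is run and reported as planned, readers will see TSAT and serum iron results confirmed by a second model that had to agree.

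The primary regressions do rest on assumptions that could be tested. One is equal residual spread in all four groups, which matters more when group sizes are 50 and 300. The Discussion gives a reason why spread might differ: it reports that clinical gestational ageing misclassifies some babies, so the groups may be mixtures. Neither named sensitivity analysis addresses this.

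**Working it through.** **1. The plan's own figure.** Inputs: 50 against 300, two-sided 0.05 (Figure 4 states a not-equal alternative), 80% power. The unadjusted detectable effect is (1.96 + 0.8416) × √(1/50 + 1/300) = 2.8016 × 0.1528 = 0.428 SD. The article states "These correspond to effect sizes of 0.35 and 0.39 respectively" for the baseline-adjusted model. With residual SD = SD × √(1 − ρ²), these values need a correlation between cord and 6–24 hour levels of √(1 − (0.35/0.428)²) ≈ 0.58 for TSAT and √(1 − (0.39/0.428)²) ≈ 0.41 for serum iron. The article gives neither correlation, so its figures fit its method but cannot be confirmed or refuted. They are not disputed here.

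**2. Joint against separate fits.** Let X be the common predictor matrix and Σ the residual covariance between outcomes. The joint generalised least-squares estimate is (Σ⁻¹⊗X′X)⁻¹(Σ⁻¹⊗X′)y = (I⊗(X′X)⁻¹X′)y. Σ cancels, leaving ordinary least squares for each outcome. The covariance is Σ⊗(X′X)⁻¹, so each outcome's SE is also the ordinary one, given the same residual divisor.

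Numerical check: 450 simulated babies (50/50/50/300), three outcomes, assumed outcome correlations 0.85 and −0.3, cord correlation 0.5.
- Groups only: largest difference about 2 × 10⁻¹⁵ in coefficients and 7 × 10⁻¹⁶ in SEs.
- All three cord levels in every equation: about 1 × 10⁻¹⁴ and 9 × 10⁻¹⁶.

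**3. Where a difference could arise** (same assumptions, SE of A vs D = 0.132).
- Primary model with the outcome's own cord level, joint model with all three: the estimate shifts with SD 0.009 (0.0092/0.132 ≈ 7% of an SE); SE ratio 1.002. The cause is the changed covariate set.
- 10% of babies dropped for missing hepcidin: the shift has SD 0.046 (about a third of an SE) and the SE rises 5%, matching 1/√0.9 = 1.054. The cause is the smaller sample.

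**4. Unequal variance.** Let k be the ratio of exposed SD to that of D (assumed), with D's SD set to 1. For A vs D in the four-group model:
- pooled variance = Σ(nᵢ − 1)sᵢ² / 446
- model SE = √[pooled variance × (1/50 + 1/300)]
- true SE = √(k²/50 + 1/300)
- type I error = 2Φ(−1.96 × model SE / true SE)

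Example, k = 1.5 in A, B and C: pooled variance = (3 × 49 × 2.25 + 299)/446 = 1.412; model SE = 0.1815; true SE = 0.2199; 1.96 × 0.1815/0.2199 = 1.618; type I error = 10.6%.

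For the pooled exposed contrast, the same steps use 150 and 300. At k = 1.5 the pooled variance is (150 × 2.25 + 300)/450 = 1.417, model SE 0.1190, true SE 0.1354, type I error 8.5%.

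| k | A vs D; A, B, C all differ | A vs D; only A differs | Pooled 150 vs 300; all differ |
|---|---|---|---|
| 0.8 | 2.7% | 2.1% | 3.5% |
| 1 | 5.0% | 5.0% | 5.0% |
| 1.25 | 8.0% | 9.7% | 6.9% |
| 1.5 | 10.6% | 14.6% | 8.5% |
| 2 | 14.4% | 23.2% | 11.0% |

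**5. Check by simulation** (A vs D, unadjusted, A, B and C sharing k, 3,000 runs). At k = 1, 1.25, 1.5 and 2, ordinary SEs rejected in 4.6%, 8.2%, 11.2% and 14.9% of runs; HC3 in 5.0%, 5.6%, 5.4% and 5.2%; Welch in 5.0%, 5.5%, 5.3% and 5.1%.

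**The case against.** **The commitment is weak and a joint model has uses.** The authors only undertake to consider it, and it gives the covariance between outcomes and a joint test. This stands, and it is why the point is minor. It does not make the model a check on the separate estimates.

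**Agreement need not be literal.** A reader might infer that the joint model must match the adjusted primary results in every digit. The article does not support that. Adjustment for the cord blood level may mean each outcome's own level, and hepcidin may be missing for some babies. Step 3 shows what follows; neither difference comes from joint modelling.

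**The variance estimator belongs to the analysis plan.** A reader might infer that unequal variance is the design's real weakness, or that leaving out robust SEs is an error. The article supports neither. It gives no group SDs, names no estimator, and an article may leave that choice to the full plan. The direction is also open: less variable exposed groups make the ordinary test conservative. The power work proceeds "assuming a lognormal distribution for the response variables TSAT and serum iron levels 6–24 hours after birth" and a log transform is allowed, which helps where spread rises with the mean. It may reduce the problem but does not test for it.

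**Type I error is the wrong measure if the spread arises because some exposed babies fail to sequester iron.** That would also raise the exposed mean, so the null hypothesis would be false. This is fair. However, the expression in step 4 also gives the non-coverage of the 95% confidence interval whatever the true difference, so the table can be read that way.

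**Larger figures for 10 against 300 are tempting.** Groups of 10 appear only as power scenarios; the target is 50 per exposed group.

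**Conclusion.** The point holds as a minor one. With a common predictor set and the same babies, the multivariate regression reproduces the separate coefficients and SEs, so it cannot show whether the TSAT or serum iron results are robust. This is algebra and needs no assumption about the data.

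The sizes for unequal variance are conditional on assumed SD ratios of 1.25, 1.5 and 2:
- A vs D, with A, B and C all more variable: about 8%, 11% and 14%.
- A vs D, with only A more variable: about 10%, 15% and 23%.
- Pooled exposed vs D, with all three more variable: about 7%, 8.5% and 11%.

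They show why equal variance is worth testing in this design. They do not show that the primary analysis is wrong.

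**What to change.** 1. Keep the multivariate model only as a joint test of the group effect on TSAT and serum iron, with or without hepcidin. State that this is its purpose and that it is not a robustness check of the separate estimates. State which cord levels enter it and how babies without hepcidin are handled.
2. Name as the sensitivity analysis the primary regressions refitted with HC3 SEs, for A, B and C each against D and for pooled exposed against D, unadjusted and cord-adjusted, on the scale chosen for the primary analysis.

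The cost is a sentence in the plan and one option in the regression command. Confidence intervals will be slightly wider if the variances are in fact equal. Sample size and data collection do not change.
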